## Abstract

Background and purpose — Knee and hip replacement are common and increasing procedures, and an optimized care process that could be implemented in different settings would be useful. The PROMISE trial investigates whether a new care process works equally in different German settings and how the results compare with current non-standardized care.

Patients and methods — This multi-center prospective mixed-method study includes 2,000 German patients receiving arthritis-related hip or knee endoprostheses. An interdisciplinary and cross-sectoral care process was developed and implemented in 3 German hospitals with different levels of care, and corresponding rehabilitation centers were included to bridge the gap after acute care.

Duration and outcome — The PROMISE trial recruited patients between May 2018 and March 2020. Follow-up will end in February 2021. Assessments are performed at: examination on clinical indication, 1 week before surgery, on the day of surgery, at the end of hospitalization, end of the rehabilitation program, and 3 months, 6 months, and 12 months after surgery. Outcomes include patient-reported outcomes, medical examination findings, and routinely collected data regarding the surgery and complications. Guideline-based interviews are conducted with selected patients and care partners. The primary endpoint is the presence of chronic pain at 12 months after surgery. Secondary endpoints are the number of recognized pre-existing conditions, physical activity at 12 months after surgery, use of medical services, quality of life, and interactions between care partners.

Trial registration — The trial is registered with the German Clinical Trials Register (https://www.drks.de; DRKS00013972; March 23, 2018).

With demographic changes joint replacement is becoming one of the most frequently performed surgeries. In Germany, approximately 175,000 total hip arthroplasties (THA) (IQTIG 2018a) and 148,000 total knee arthroplasties (TKA) (IQTIG 2018b) are performed each year.

These replacement procedures are associated with various risks and complications, including infection and thrombosis, as well as a considerable financial burden. Moreover, 7% to 23% of patients with THA and 10% to 34% of patients with TKA report an unfavorable long-term outcome (Beswick et al. 2012). Due to the high number of these interventions, clinical, patient-centered, and economic results might be improved by even minor advancements in the treatment process. In Germany no generally applicable evidence-based treatment standard has yet been developed. Thus, the current care system does not achieve its full potential, including the cost–benefit ratio.

The PROMISE trial aims to improve the care process in Germany based on the principles of the Enhanced Recovery after Surgery Society (ERAS). An ERAS path is defined to optimally prepare the patient for an intervention with minimized stress and stress reactions, maintained homeostasis, and avoiding catabolism that leads to loss of protein, muscle strength, and cellular dysfunction (Ljungqvist 2012). The ERAS approach has been applied to numerous elective procedures and provides approximately 30–50% reductions in the complication rate and length of stay (Ljungqvist et al. 2017). Because of a call for certified intersectoral centers to improve the quality of care (IGES Institut 2016), the PROMISE study involves 3 hospitals with different levels of care, including all required departments, as well as 5 inpatient and outpatient rehabilitation centers. Standard operating procedures defined by an interdisciplinary panel, and a central database for continuous evaluations, audits, and improvements (Ljungqvist et al. 2017) aim to minimize loss of potential effectiveness due to insufficient coordination, lack of common therapeutic goals, incomplete information flow, and separate data collection.

## ^Patients and methods^

### ^Study design^

The PROMISE trial is a prospective multi-center mixed-method study, including patients with an indication to undergo surgery (THA or TKA) at 3 German hospitals (a regional hospital, an orthopedic-specialized hospital, and a tertiary referral university hospital). The PROMISE process involves standardized indication criteria for intervention (Schmitt et al. 2017), preoperative screening for psychological (Gylvin et al. 2016) and geriatric risk factors (Gronewold et al. 2017), blood management (Vaglio et al. 2016), preoperative patient education (Edwards et al. 2017), no preoperative fasting (Smith et al. 2011), postoperative nausea and vomiting prophylaxis (De Oliveira et al. 2013), maximum soft-tissue-sparing techniques (Ljungqvist et al. 2017), intraoperative bleeding and swelling management (Guler et al. 2016, Nielsen et al. 2016), avoidance of suction drainage (Kelly et al. 2014), bladder catheters (Huang et al. 2015), and intravenous catheters (Sharma et al. 2010), local infiltration analgesia (Yun et al. 2015), multimodal oral pain therapy (Khan et al. 2014), starting rehabilitation on the day of surgery (Okamoto et al. 2016), functional discharge criteria (Hansen 2017), and intensified rehabilitation (DRV 2016). All patients are followed for up to 12 months after surgery. Data are collected by medical staff at the time of examination on indication, during patient education, at surgery, at hospital discharge, at the end of rehabilitation, and at 12 months after surgery. Patient-reported outcome measurements are obtained before surgery, at hospital discharge, and at 3 months, 6 months, and 12 months after surgery. Regarding secondary endpoints, a control group will be used consisting of patients from a German health insurance database. Patients will be matched according to age, sex, and diagnosis. To limit the number of survey-based instruments and patient burden, we conducted guideline-based interviews with 10 randomly selected patients to identify aspects that are difficult to capture using a quantitative approach. Interviews have been also conducted with different care partners (e.g., physicians and physiotherapists) to identify and address potential burdens.

### ^Study subjects and eligibility criteria^

Patients indicated for joint replacement due to arthritis of the hip or knee are eligible for study participation. Patients are enrolled if they have met standardized criteria for surgery (Schmitt et al. 2017) and if they are able to understand the nature and extent of the study.

*Exclusion criteria are:* life expectancy less than 1 year (e.g., advanced cancer), any conditions that might preclude elective surgical intervention, and medical or psychological factors that would prevent them from participating or providing informed written consent.

### ^Patient withdrawal^

Patients can withdraw their consent without giving reasons at any time during the trial without disadvantage. No additional data will be collected after that point, although any existing data will remain in the study database. Patients who withdraw are not replaced.

### ^Intervention^

The optimized PROMISE care process consists of interrelated measures (Figure 1). The ERAS Society guidelines (Wainwright et al. 2019) are evidence-based, although we complement those guidelines with non-evidence-based measures to avoid unnecessarily restricting the process optimization. These non-evidence-based measures are derived from a basic understanding of process optimization to avoid stress and promote activity.

**Figure 1. F0001:**
[figure not shown]
Schematic representation of the treatment process. PROMISE-specific procedures are shown in the red boxes. MRSA: methicillin-resistant *Staphylococcus aureus*.

### ^Indication for surgery^

The indication for surgery requires appropriate radiological findings, intolerable pain or suffering, restriction of activity, and exhaustion of nonoperative options (Schmitt et al. 2017). The patients define their activity or participation goals throughout the process.

### ^Preoperative screening for concomitant previous conditions^

Anemia is identified using the laboratory values for hemoglobin, ferritin, transferrin saturation, blood cell counts, red blood cell morphology, glutamic pyruvic transaminase, glutamic oxaloacetic transaminase, bilirubin, C-reactive protein, and reticulocytes. If necessary, iron is administered (orally or intravenously). Screening is performed to identify seniors at risk (ISAR screening) and psychosomatic risk (Patient Health Questionnaire-4 [PHQ-4], Oslo Social Support Scale [OSSS], Somatic Symptom Disorder [SSD], Life-Orientation-Tests [LOT-R]). Preoperative screening for thrombosis and bleeding risk is based on previous deep vein thrombosis or pulmonary embolism, known coagulation disorder/thrombophilia, venous thromboembolism in immediate relatives, previous severe bleeding, cancer within the last 5 years, and varicose veins. Specialized co-care is permitted if required.

### ^Patient education^

Patients are educated preoperatively by all involved professional groups. This process also involves discussing the patien’s tasks and co-responsibilities. Patients are also motivated to find a personal coach who supports the patient’s active role in the care process.

### ^Additional preparations^

Preoperative preparations include providing the patient with crutches and guidance regarding walking, using stairs, as well as instructions regarding preoperative fitness training. Patients also receive counseling regarding the rehabilitation options and programs (outpatient or inpatient).

### ^Immediately before surgery^

Medication for anxiolysis is avoided if possible. A light meal can be consumed up to 6 hours, and small amounts of clear liquids can be drunk up to 2 hours before anesthesia induction. Etoricoxib (90 mg) is administered 90 minutes and antibiotic (cefazolin 2 g i.v.) 30 minutes before the skin incision, followed by 1 g of tranexamic acid to reduce blood loss.

### ^During surgery^

General anesthesia and spinal anesthesia can be used. A single intraoperative steroid injection (e.g., 20 mg of dexamethasone or 125 mg of methylprednisolone) is used to attenuate the surgical stress response, improve analgesia, and reduce postoperative nausea and vomiting. The surgical technique aims to minimize trauma using the smallest possible incisions and natural muscle gaps. To prevent dislocation, the implanted THA must tolerate at least 30° internal rotation at 90° flexion and at least 70° external rotation in 0° extension. Local infiltration analgesia involves administration of ropivacaine (0.2%, 150 mL) with adrenaline (0.5mg/150mL) and an additional 50 mL of plain ropivacaine (0.2%) subcutaneously. Use of suction drainage and bladder/intravenous catheters is avoided whenever possible.

### ^Rehabilitation^

There are generally no restrictions regarding load bearing and range of motion. The patient begins independently leaving their bed and walking with crutches on the day of surgery, with support from the nursing staff or physiotherapist as necessary to achieve independent basic functions (changing position, personal hygiene, dressing and undressing, and eating at a table). Thromboprophylaxis is performed using low molecular weight heparins in weight- and risk-adapted dosage starting on the first postoperative day. In compliance with national guidelines thromboprophylaxis is continued for 35 (THA) or 14 (TKA) days postoperatively. Opioid use is minimized, and basic medication is used during days 3–8 (etoricoxib at 90 mg orally in the morning and metamizole 4 x 1 g). After day 8, the only medication is etoricoxib (90 mg orally in the morning). The patient is discharged to home or a rehabilitation facility when the wound is dry, pain is tolerable, and they can independently perform basic functions (change position, personal hygiene, dressing and undressing, walking > 150 m, and climb 10 steps). Patients who are discharged home also complete rehabilitation programs that comply with the rehabilitation therapy standards of the German Pension Insurance (DRV 2016).

### ^Endpoints^

#### Primary endpoint

The primary endpoint is presence of chronic pain at 12 months after surgery, evaluated with the pain subscore from the Western Ontario and McMaster Universities Osteoarthritis Index (WOMAC). Approximately 9% of patients report pain at 12 months after surgery (Beswick et al. 2012) and the evaluation is planned using a 2-sided binomial test. The WOMAC is calculated using the hip osteoarthritis outcome score (HOOS) (Klässbo et al. 2003) or the knee osteoarthritis outcome score (KOOS) (Roos et al. 2003).

#### Secondary endpoints

The secondary endpoints are number of recognized pre-existing conditions (as proxy we use pre-existing anemia) at baseline, physical activity at 12 months after surgery, use of medical services during the 12 months after surgery, quality of life at 12 months after surgery, and interactions between care partners during the 12 months after surgery. Physical activity is evaluated using the HOOS/KOOS subscore HOOS-PS/KOOS-PS (physical function short form) for THA/TKA cases, with data collected before the surgery and at 3 months, 6 months, and 12 months after the operation. Quality of life at 12 months after surgery is assessed using patient-reported scores from the EQ-5D-5L (Conner-Spady et al. 2015) and the EQ-5D visual analogue scale (VAS) on a 0–100 numeric scale. This data is also collected before surgery and at 3 months, 6 months, and 12 months after surgery.

Type and frequency of use of medical service during the 12 months after surgery is evaluated using a questionnaire. The results will be compared with results from a control group of patients from a German health insurance database who are matched according to age, sex, and diagnosis/treatment history. Statistical power for those analyses will be improved by matching 1 PROMISE participant to 4 control individuals. Cost analyses will also be performed to compare the PROMISE and control groups, to identify potential savings. Interactions between care partners during the first 12 months after surgery are also considered to determine whether a stable plateau is reached in the number of intersectoral interactions for each patient. The interviews will be evaluated according to the qualitative content analysis described by Mayring (2000).

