### ^Estimated sample size and power^

The estimated sample size is based on the primary endpoint (chronic pain at 12 months), which will be evaluated using a 2-sided binomial test. A previous report has indicated that approximately 9% of patients report chronic pain after 1 year (Beswick et al. 2012). Thus, 1,900 patients are required to detect a 20% reduction (i.e., from 9% to 7.2%) based on an α level of 5% and power of 80%. Assuming 5% of patients will be lost to follow-up, the target sample size is 2,000 participants. This sample size also provides power of > 80% for analyzing the 2 confirmatory secondary endpoints (number of anemia cases and physical activity after 1 year; values selected from the literature), which will be analyzed only if a significant improvement is observed in the primary endpoint.

The secondary analyses are based on non-inferiority tests and previously reported values. The number of anemia cases will be tested to determine whether it is ≤ 2% below the expected reference value of 15.5% for Central Europe (McLean et al. 2009). Physical activity will be tested using the HOOS-PS/KOOS-PS to determine whether the patients achieve at least the minimum clinically important improvement (23 points) (Paulsen et al. 2014). To comply with the α-error, confirmatory testing for these 2 secondary endpoints will be performed only if statistically significant improvement is observed for the primary endpoint. To evaluate the achievement of a plateau in the number of interactions between care partners, the implementation period is divided into 3 intervals. The number of interactions in intervals II and III will be tested for equality. The criterion for equality will be based on the difference between the 1st and 2nd intervals. Poisson models will be used to compare the numbers of healthcare interactions between PROMISE participants and the control group, with sub-analyses according to different cost categories (e.g., hospital stays vs. general practitioner visits). Factors that potentially influence healthcare utilization, interactions, and quality of life will be evaluated using hierarchical regression models with care partners considered as clusters.

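### Service use is patient-reported in PROMISE but taken from an insurance database in the controls, so any effect on use or cost is confounded with data source, in unknown direction

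*Protocol article*

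**What the plan says.** **PROMISE group.** Under Secondary endpoints: "Type and frequency of use of medical service during the 12 months after surgery is evaluated using a questionnaire". The data collection table lists a cost book at the hospital stay and at the 3-, 6- and 12-month follow-ups and flags it as patient-reported.

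**Control group.** The next sentence under Secondary endpoints begins: "The results will be compared with results from a control group of patients from a German health insurance database". The ratio is fixed by "matching 1 PROMISE participant to 4 control individuals", which the article justifies by statistical power.

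**Matching variables.** These are given twice and differently. Study design has: "Patients will be matched according to age, sex, and diagnosis". Secondary endpoints has controls "compared with results from a control group of patients from a German health insurance database who are matched according to age, sex, and diagnosis/treatment history".

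**Analysis.** Under Estimated sample size and power: "Poisson models will be used to compare the numbers of healthcare interactions between PROMISE participants and the control group", with sub-analyses by cost category. Under Secondary endpoints: "Cost analyses will also be performed to compare the PROMISE and control groups, to identify potential savings".

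**What is acknowledged.** The Discussion concedes that randomisation was not feasible and that the matched cohort is only a partial remedy. It does not mention that the two groups' use comes from different sources.

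**The concern.** In one group the patient reports the contacts; in the other they are what an insurer's database holds. Every PROMISE patient is measured one way and every control the other, so no covariate in a Poisson model can separate a care effect from a reporting difference. More controls do not help, because a systematic difference does not shrink with sample size.

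The groups may also differ as patients. PROMISE participants gave consent, met standardised surgical criteria and exclude those expected to live less than a year; the article states no such filter for controls. Comorbidity is collected at baseline in PROMISE but is not named as a matching variable.

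At stake is the interpretation of any difference in use and of any savings figure. The Discussion also offers this matched comparison as its partial answer to the lack of a randomised control group.

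**Working it through.** **1. The plan's own figures.** The article gives no power or precision figure for the use comparison, so the group sizes come from the primary endpoint. For a one-sample two-sided binomial test of 9% against 7.2%:

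n = [(1.96 × √(0.09 × 0.91) + 0.842 × √(0.072 × 0.928)) / 0.018]² ≈ 1,871

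Exact power at 1,900 is 80.6%, and 1,900 / 0.95 = 2,000. The stated sample size reproduces and is not in dispute. At 1:4, the 1,900 evaluable participants correspond to 4 × 1,900 = 7,600 controls.

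**2. What the comparison can identify.** Let r be the completeness of recording in PROMISE divided by completeness in the controls. Then

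observed rate ratio = true rate ratio × r.

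Only the product is observed. A ratio of 0.95 fits a true ratio of 0.95 with r = 1, a true ratio of 1 with r = 0.95, or a true ratio of 1.05 with r = 0.95/1.05 = 0.905. No passage provides information on r: the article plans neither insurer records for participants nor a check of the questionnaire against them. The interface in Data quality assurance imports hospital quality data and does not mention outpatient contacts.

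**3. Illustration of size.** All inputs except the group sizes are assumptions from outside the documents: mean 10 contacts a year, variance 60 (variance/mean ratio 6), no true effect, Wald test of the log rate ratio at two-sided 5%.

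SE = (√60 / 10) × √(1/1,900 + 1/7,600) = 0.7746 × 0.02565 = 0.0199

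| Reporting error in PROMISE | ln r | z | Declared significant |
|---|---|---|---|
| 5% under | −0.0513 | −2.58 | about 73% |
| 10% under | −0.1054 | −5.30 | over 99.9% |
| 5% over | +0.0488 | +2.46 | about 69% |

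For the first row, the chance is Φ(2.58 − 1.96) = Φ(0.62) ≈ 0.73.

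**4. Effect of the matching ratio.** With 1:1 matching and the same assumptions, SE = 0.7746 × √(2/1,900) = 0.0251 and z = −0.0513/0.0251 = −2.04, giving Φ(0.08) ≈ 53%. Going to 1:4 raises this to 73%; the bias stays at 5%.

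**5. Sensitivity to the assumptions.** For 5% under-reporting at 1:4, with SE = √[φ × (1/(1,900 × λ × 0.95) + 1/(7,600 × λ))], mean λ and variance/mean ratio φ:

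| λ | φ | Declared significant |
|---|---|---|
| 1 | 3 | 20.5% |
| 1 | 1 | 50% |
| 5 | 3 | about 72% |
| 10 | 3 | about 95% |
| 5 | 1 | about 99% |

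The result depends on φ/λ. The case λ = 5, φ = 3 has the same value (0.6) as the case in step 3, so their agreement is not independent support.

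**6. Matching and eligibility, side by side.** Study design names age, sex and diagnosis. Secondary endpoints adds treatment history as part of, or alternative to, diagnosis, and does not define it. Neither names comorbidity, which Data collection lists as a baseline item. The hierarchical regression under Estimated sample size and power concerns factors that influence utilisation and is not described as adjusting the PROMISE–control contrast.

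**The case against.** The strongest reply is that much of this is acknowledged, provisional or exploratory. The Discussion admits the non-randomised design. Use of services is not one of the two confirmatory secondary endpoints. Sub-analyses by cost category are already planned. Treatment history may carry prior care, and covariates and control-selection codes are commonly left to an analysis plan that is not shown. The cost book is completed repeatedly and may work as a diary, so under-reporting could be small. This stands as far as it goes: it limits the weight of the point, and the lack of detail on covariates is not by itself a fault. It does not answer the source mismatch, which the article itself fixes by naming both the instrument and the comparator.

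A reader might go further and infer that the bias must make PROMISE look cheaper. The documents do not support that. Forgotten contacts would lower PROMISE counts, but patients may also report services that an insurer does not hold, and the article does not say what the database covers. Rehabilitation follows German Pension Insurance standards and funding agencies choose the facility, so part of it may be absent from the controls' data, which would make controls look cheaper. Selection is equally open: the indication requires severe symptoms and failed conservative treatment, and one site is a tertiary university hospital.

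A reader might also take this to be the only concurrent comparison, or matching to be on age, sex and diagnosis alone. The control period is not stated, and Secondary endpoints gives a wider matching rule than Study design.

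**Conclusion.** The point holds as a confounding of group with data source that the article does not acknowledge. Any effect of the care process on use or cost is mixed with reporting differences of unknown size and direction, and 1:4 matching does not remove them. It would be too strong to say the comparison measures nothing but data source and selection; a care effect may be present but cannot be isolated.

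The mismatch rests on the article's text, with one inference: that the controls' use is what the insurance database records. The 73% figure is illustrative only. For 5% under-reporting, the scenarios shown run from 20.5% to about 99%. The primary endpoint and the stated sample size are unaffected. The change is worth making because it is cheap relative to the savings statement that depends on it.

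**What to change.** 1. Limit inferential comparisons of use and savings to categories confirmed to be recorded comparably in both sources; hospital stays, readmissions and revision surgery are candidates. The planned split by cost category provides the structure.
2. Report other contacts descriptively, dividing the observed rate ratio by a range of r on both sides of 1 (for example 5% to 30% under- and over-reporting, as a working assumption), and state the r at which the conclusion changes.
3. Match or adjust the PROMISE–control contrast also on joint, coded comorbidity and year of surgery, and apply to controls those PROMISE exclusions that codes can identify.
4. State one matching rule in Study design and Secondary endpoints, and define treatment history if it is kept.
5. Name the source mismatch as a limitation beside the lack of randomisation.
6. Optionally, where existing consent and data protection allow, use participants' insurer records as the common source or to validate the questionnaire. Recruitment closed in March 2020 and the article states no consent for linkage, so this may not be cheap and the other steps should not depend on it.

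Cost: analysis wording and a revised data request for items 1 to 5, with no new patients or visits. The price is fewer comparable cost categories and somewhat fewer matched controls.
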